## Methods/design

### Objective

We propose a multi-center randomized controlled clinical study to demonstrate the efficacy and safety of *Buzhong Yiqi* decoction in the treatment of MDRO HAP and to explore the possible mechanism, provide a reliable evidence-based rationale for the treatment of MDRO pulmonary infection with TCM, further elucidate the scientific notion of “treating different diseases with the same method”, and expand the modern disease spectrum of *Buzhong Yiqi* decoction. We do this to open up new ideas and methods for MDRO prevention and treatment strategies and formulate TCM diagnosis and treatment regimens for pulmonary infections caused by MDROs in clinical practice.

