### Sample size

Considering that no previous studies have been conducted to calculate the sample size, and assuming that the withdrawal rate is less than 15% [23], we expect that 100 patients will be enrolled in each arm, and that the final sample size of each arm will be at least 85. The data we collect will be helpful to calculate the appropriate sample size in the future and provide reference for further large-scale research.

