### Statistical analysis

#### Data analysis

The Longhua Hospital Shanghai University of Traditional Chinese Medicine will be in charge of data management and statistical analysis in this study. Statistical analysts are not involved in clinical observation; they are responsible for statistical analysis of study data and timely delivery of statistical reports to the study director. Statistical analysis will be performed with SPSS 20.0 software. Measurement data are expressed as mean ± standard deviation. Normality test and homogeneity test of variance will be performed first. In case of normal distribution and homogeneity of variance, a *t*-test is performed, otherwise a non-parametric test is used. Count data are expressed as frequency constituent ratio (percentage) and *X*^*2*^ test is performed. *P* < 0.05 indicates statistical significance.

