## Discussion

Infections caused by drug-resistant bacteria have become a major problem that seriously threatens the health of Chinese people and impacts national medical finance. It is of great scientific and clinical significance to actively carry out research on the prevention and treatment of MDRO infections. With the extensive use of broad-spectrum antibiotics in clinical practice, the problem of bacterial resistance is becoming more and more serious [24–26]. The *Enterobacteriaceae* in an Indian outbreak in 2010 were resistant to all the available antibiotics, which attracted global attention [27]. On January 29, 2018, the World Health Organization (WHO) published monitoring data on bacterial resistance to antibiotics for the first time, which revealed that bacterial resistance was widespread, with serious bacterial infections and high drug resistance in both high- and low-income countries, and had become a major public health problem worldwide [28].

By analyzing the clearance of drug-resistant pathogens, APECHA II score, CPIS score, TCM diagnostic and therapeutic criteria, mortality and related physical and chemical indicators, this study may confirm the clinical safety and efficacy of *Buzhong Yiqi* decoction in the treatment of MDRO HAP. In addition, by analyzing CRP, platelets, blood lactic acid, procalcitonin, and coagulation function, we will reveal the possible anti-inflammatory mechanism of *Buzhong Yiqi* decoction in treating MDRO HAP. Finally, if the hypothesis of this study is proved to be true, it can not only provide a clinical basis for the theory of “acute *Qi* deficiency” for HAP caused by MDRO, but also enrich the theory and practice of treating infectious diseases with TCM. Additonally, it is important to form a clinical diagnosis and treatment plan or guidance for comprehensive treatment of MDRO HAP with TCM, so as to reduce the medical and financial burdens caused by infections.

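### The primary outcome has four ordered grades, but the only method stated for such data is a chi-square test read at P < 0.05, which ignores the order, gives no effect size or direction, and loses power

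*Protocol article*

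**What the plan says.** All references are to the protocol article.

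- **Primary outcome (Efficacy evaluation criteria in TCM).** Each patient is placed in one of four grades by the syndrome efficacy rate: at least 90% (clinical control), 60% to under 90% (excellent), 30% to under 60% (effective), and under 30% (not effective). The grades run from best to worst.
- **Data analysis.** Measurement data are summarised by mean and standard deviation and compared by t-test or, failing normality or equal variance, a non-parametric test. Count data are summarised by frequency and percentage and compared by chi-square. The decision rule is P < "0.05 indicates statistical significance". No between-arm effect measure or interval is named here or elsewhere in the article.
- **Sample size.** The number is not derived from an effect or a power: "Considering that no previous studies have been conducted to calculate the sample size". The plan is that "100 patients will be enrolled in each arm, and that the final sample size of each arm will be at least 85". The stated use of the data is modest: "The data we collect will be helpful to calculate the appropriate sample size in the future and provide reference for further large-scale research".
- **Objective and Discussion.** The aim is "to demonstrate the efficacy and safety of" the decoction, and the Discussion says that "this study may confirm the clinical safety and efficacy of" the decoction.

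**The concern.** The four grades are categorical, and the non-parametric option is offered only for measurement data. As written, the primary comparison is therefore a chi-square test on a 2 × 4 table with 3 degrees of freedom. That test asks whether the two arms differ in any way across the grades. It does not ask whether patients on the decoction tend to reach better grades, which is the clinical question.

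Two things are at stake. First, power is spread over three degrees of freedom when the expected effect is a shift in one direction, so a real benefit is more easily missed. Second, the test result does not say how large the effect is, or which arm it favours. That matters more here than in a powered trial. Since no target effect was set, P above 0.05 is weak evidence of no effect, and P below 0.05 does not say whether the effect is worth having. The Objective and Discussion nevertheless look for a conclusion about efficacy.

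**Working it through.** **The plan's own figure.** 100 × (1 − 0.15) = 85 per arm, from 100 enrolled and "assuming that the withdrawal rate is less than 15" per cent. This reproduces. No power figure is stated, so there is none to reproduce.

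**Inputs.** From the article: n = 85 per arm, four ordered grades, significance level 0.05 (taken as two-sided, since the article does not say). Assumed: control-arm grades from best to worst 10%, 25%, 35%, 30%, and a common odds ratio (OR) of 2 for being in a better grade.

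**Step 1: decoction-arm distribution.** Control cumulative proportions from the best grade are 0.100, 0.350 and 0.700. Multiplying each cumulative odds by 2 gives 0.182, 0.519 and 0.824, so the four grades become 0.182, 0.337, 0.305 and 0.176.

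**Step 2: chi-square power.** Noncentrality λ = n Σ (p − q)²/(p + q), where p and q are the grade proportions in the two arms.

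λ = 85 × (0.02375 + 0.01281 + 0.00309 + 0.03203) = 85 × 0.07168 = 6.09.

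With 3 degrees of freedom and critical value 7.815, power is 0.525, or about 53%.

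**Step 3: ordinal power.** The information on log OR is approximately V = (n/6)(1 − Σ p̄³), where p̄ is the mean of the two arms in each grade.

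V = (85/6)(1 − 0.0767) = 13.08. Then z = ln 2 × √13.08 − 1.96 = 2.507 − 1.96 = 0.547, and power is 0.71.

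Simulating 100,000 trials gave 0.53 for chi-square and 0.70 for the rank test.

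**Step 4: smaller effect.** At OR = 1.7, λ = 3.61 gives 33% for chi-square. V = 13.05 gives 48% for the ordinal analysis.

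**Step 5: sensitivity to the assumed grades.** Nine control distributions were tried, with the lowest grade holding 10% to 40% of patients. Simulated power was:

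| Common OR | Chi-square, 3 df | Rank test |
|---|---|---|
| 2.0 | 51–53% | 69–71% |
| 1.7 | 31–33% | 47–48% |

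**Step 6: what each analysis reports.** Take invented counts of 85 per arm, best to worst: control 10, 20, 30, 25; decoction 18, 27, 25, 15.

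- Chi-square with equal arms: Σ (a − b)²/(a + b) = 64/28 + 49/47 + 25/55 + 100/40 = 2.29 + 1.04 + 0.45 + 2.50 = 6.28, P = 0.099. Shuffling the grade labels or swapping the arms leaves 6.28 unchanged.
- Proportional-odds model on the same counts: common OR 2.02, 95% CI 1.16 to 3.49, P = 0.013. The rank test also gives P = 0.013.

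**Step 7: uncertainty that a P value leaves out.** At 85 per arm the 95% half-width for a difference in percentages is at most 1.96 × √(2 × 0.25/85) = 15.0 points. For a difference in means it is 1.96 × √(2/85) = 0.30 SD. For the common OR, the interval multiplies and divides the estimate by exp(1.96/√13.08) = 1.72.

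**The case against.** The strongest objection is that this is a condensed article. Effect measures and confidence intervals are commonly left to the full protocol or the SAP, neither of which is shown. That stands: the lack of intervals is not by itself a finding. What remains is a method the article does state. It assigns categorical data a chi-square test and a P < 0.05 rule, and that method fits an ordered outcome badly.

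A second objection is that percentages by grade will stand beside the P value, so a reader can see the direction and work out an effect and its interval. That also stands in part. It does not recover the lost power, and it leaves the choice of effect measure to be made after the results are seen.

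A third is that the grades might be collapsed to effective (at least 30%) against not effective, where chi-square is a sound test. The article does not say so, and collapsing would not restore power. With the distribution above it compares 70.0% with 82.4%. The null standard error is √(2 × 0.7618 × 0.2382/85) = 0.0653, and the alternative standard error is √((0.2100 + 0.1453)/85) = 0.0647. Then (0.1235 − 1.96 × 0.0653)/0.0647 = −0.07, or about 47% power.

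A fourth is that the ordinal gain depends on an effect that moves patients consistently towards better grades. If it moved them in both directions, chi-square could do better. That is correct, but an overall shift is what the efficacy aim implies.

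A reader might infer more than the documents support:

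- **That the trial cannot serve to size a later one.** The Sample size section says only that the data will help, and the planned standard deviations and percentages are inputs such a calculation uses.
- **That the results will be misread.** This is a prediction. The text supports only a risk, raised by the wording of the Objective and Discussion.
- **That the observed difference will be biased upward.** A difference between randomised arms is not biased upward unless it is selected for significance, and nothing in the article says it will be.

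**Conclusion.** The point holds for the stated analysis of the primary outcome. Chi-square on four ordered grades discards their order and carries no size or direction. For a consistent shift at 85 per arm, it gives up about 17 percentage points of power at a common odds ratio of 2 (53% against 70%) and about 15 at 1.7 (33% against 48%). These figures rest on assumed grade distributions, proportional odds and a two-sided 0.05 level. The loss changed little over the nine distributions tried.

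The broader part is a matter of fit between sections. With no effect or power behind the sample size, a P < 0.05 verdict alone is a weak basis for the efficacy conclusion that the Objective and Discussion look for. This does not extend to saying that the trial fails its stated purpose, or that the sponsor has ruled out reporting estimates. No number stated in the article is wrong on this point.

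**What to change.** In Data analysis, name the primary analysis separately from the general rule for count data:

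- Compare the four grades by a proportional-odds model and report the common odds ratio with its 95% CI. State in advance how the proportional-odds assumption will be checked, and that a rank test with a matching effect estimate and interval will be used if it fails.
- Base the primary conclusion on that estimate and interval, not on whether P is below 0.05.
- For the other comparisons, report the between-arm difference (risk difference, or mean or median difference) with a 95% CI beside each P value.

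Align the Objective and Discussion with the Sample size section, so that the strength of the efficacy claim matches a sample with no power basis.

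The cost is a few sentences of analysis wording, fixed before outcome data by arm are seen, plus the assumption check. It needs no new data, visits or site work, and the sample size is unchanged.

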#### Consent

Patients who meet the study requirements will be offered a consent form covering the study name, registered information, research background, how the study is to be conducted, what participants should do in the study, inclusion/exclusion criteria, treatment plans and obligations, possible drug-related side effects, expenses during participation, etc. We will make every effort to protect the privacy of patients’ personal medical data to the extent permitted by law. Participation in this study is completely voluntary, and other treatment options will be offered to patients who do not participate or drop out. When patients sign the informed consent form, their personal and medical information will be used in this study.

#### Confidentiality

Participants’ medical records will be kept at the hospital, and the investigator, the research authority, and the ethics committee will be allowed access to these medical records. Any public report on the results of this study will not disclose participants’ personal identities. We will make every effort to protect the privacy of participants’ personal medical data to the extent permitted by law. Personal and medical information will be kept confidential in a safe and reliable place. At any time, participants may request access to their personal information (such as address, contact information, etc.) and may modify this information if necessary.

## Discussion

Infections caused by drug-resistant bacteria have become a major problem that seriously threatens the health of Chinese people and impacts national medical finance. It is of great scientific and clinical significance to actively carry out research on the prevention and treatment of MDRO infections. With the extensive use of broad-spectrum antibiotics in clinical practice, the problem of bacterial resistance is becoming more and more serious [24–26]. The *Enterobacteriaceae* in an Indian outbreak in 2010 were resistant to all the available antibiotics, which attracted global attention [27]. On January 29, 2018, the World Health Organization (WHO) published monitoring data on bacterial resistance to antibiotics for the first time, which revealed that bacterial resistance was widespread, with serious bacterial infections and high drug resistance in both high- and low-income countries, and had become a major public health problem worldwide [28].

By analyzing the clearance of drug-resistant pathogens, APECHA II score, CPIS score, TCM diagnostic and therapeutic criteria, mortality and related physical and chemical indicators, this study may confirm the clinical safety and efficacy of *Buzhong Yiqi* decoction in the treatment of MDRO HAP. In addition, by analyzing CRP, platelets, blood lactic acid, procalcitonin, and coagulation function, we will reveal the possible anti-inflammatory mechanism of *Buzhong Yiqi* decoction in treating MDRO HAP. Finally, if the hypothesis of this study is proved to be true, it can not only provide a clinical basis for the theory of “acute *Qi* deficiency” for HAP caused by MDRO, but also enrich the theory and practice of treating infectious diseases with TCM. Additonally, it is important to form a clinical diagnosis and treatment plan or guidance for comprehensive treatment of MDRO HAP with TCM, so as to reduce the medical and financial burdens caused by infections.

### Trial status

Protocol version 1, 11 February 2018.The recruitment commenced in July 2018 and aims to enroll 200 participants for the trial. It is anticipated that recruitment will end by June 2021.

## Data Availability

Not applicable.

## Abbreviations

CPIS: Clinical pulmonary infection score
CRF: Case report form
eCRF: Electronic case report form
EDC: Electronic data capture
HAP: Hospital acquired pneumonia
ICU: Intensive care unit
MDRO: Multi-drug resistant organisms
TCM: Traditional Chinese medicine
VAP: Ventilatilator-associated pneumonia
